#### MRI analysis

Neuroimaging data from all tasks will be analysed using various neuroimaging software packages, including FSL, SPM, (Turbo-) Brainvoyager, Nipype, as well as custom analysis scripts. The data will be first pre-processed, to remove artefacts, such as movement and physiological noise. General Linear Models will then be used per participant, per task, with regressors representing task activity, as well as nuisance parameters such as motion parameters and physiological noise parameters. Parameter estimates will then be introduced into second level a mixed-effect model with group (MBSR, wait-list), and time (baseline, post-treatment) as fixed factors, as well as a group x time interaction. Additional fixed factors will be added (university, sex, age, and recruitment wave). A random intercept for participants will be included to account for individual differences. In all tasks we will assess brain connectivity patterns of three large-scale brain networks (SN, ECN, DMN). Connectivity will be operationalised as the correlation coefficients between activity time-courses of nodes of these networks. Within- and between-network connectivity will be calculated to determine network cohesion and between-network communication, respectively. Potential connectivity patterns we observe (e.g., changes in SN or ECN within-network connectivity) will be tested as potential moderators of the clinical outcome post-treatment.

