**Methods:**

This study is a longitudinal two-arm randomised, wait-list controlled trial to investigate the effects of MBSR on a preselected, Dutch university student population with elevated stress levels. Clinical symptoms are measured at baseline, post-treatment, and three months after training. Our primary clinical symptom is perceived stress, with additional measures of depressive and anxiety symptoms, alcohol use, stress resilience, positive mental health, and stress reactivity in daily life. We investigate the effects of MBSR on stress regulation in terms of behaviour, self-report measures, physiology, and brain activity. Repetitive negative thinking, cognitive reactivity, emotional allowance, mindfulness skills, and self-compassion will be tested as potential mediating factors for the clinical effects of MBSR. Childhood trauma, personality traits and baseline brain activity patterns will be tested as potential moderators of the clinical outcomes.

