Thus, the goals of the current study are to (1) establish clinical effects of MBSR in a population of Dutch university students with high levels of perceived stress, (2) identify the effect of MBSR on stress regulation, (3) assess the role of large-scale networks in this process, and (4) identify for whom MBSR might be more beneficial. Our main hypothesis regarding aim (1) is that MBSR is effective at reducing self-reported perceived stress in a population of highly stressed university students, sustained over a 3-month follow-up period. We expect to replicate previous studies showing the efficacy of MBSR within student populations [30–33] and we expect that MBSR is also effective at reducing other relevant clinical symptoms in this population, such as depression and anxiety symptoms [9]. Regarding aims (2) and (3) (i.e., the effects of MBSR on stress regulation and the role of large-scale networks in this process), we hypothesise that MBSR leads specifically to concurrent enhancement of cognitive control *and* affective processing across the different domains of stress-regulation described above. Moreover, we expect that these measures at baseline will be important in predicting individual differences in effectiveness of MBSR, and that changes in these measures will be accompanied by changes at the clinical level for aim (4).

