## Methods

### Design

This study is a two-arm randomised, wait-list controlled trial with ethical approval from the local medical-ethical committee (METC Oost-Nederland), see Fig. 1. Participants are randomised into a treatment and a wait-list control group after baseline measurements including clinical, neurocognitive, and ecological momentary assessments. In the following two months, the treatment group participates in an MBSR training, and the wait-list group receives no planned intervention for two months, serving the purpose of assessing the effect of the intervention on the study outcomes against not receiving treatment during the same time-period. Post-treatment measurements take place three months after baseline, and they include another set of clinical, neurocognitive, and ecological momentary assessments. Six months after baseline there is a follow-up clinical assessment. After this assessment, the participants in the wait-list group receive the MBSR training, after which they complete a final clinical assessment.

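### The MRI analysis names changes in brain connectivity as moderators; on the natural reading these are post-randomisation variables that MBSR may alter, so they cannot show for whom it works

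*Protocol article*

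**What the plan says.** The article describes the brain moderators in three places.

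- **Abstract, Methods:** "Childhood trauma, personality traits and baseline brain activity patterns will be tested as potential moderators of the clinical outcomes".
- **Background, aims and hypotheses:** aim 4 is to "identify for whom MBSR might be more beneficial". For this aim the authors write "we expect that these measures at baseline will be important in predicting individual differences in effectiveness of MBSR". The same sentence adds a second expectation, that change on these measures goes along with clinical change.
- **Statistical analysis, MRI analysis:** "Potential connectivity patterns we observe (e.g., changes in SN or ECN within-network connectivity) will be tested as potential moderators of the clinical outcome post-treatment".

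The Clinical symptoms section assigns the roles differently for questionnaires. Changes in repetitive negative thinking, mindfulness skills and similar scores are candidate mediators of PSS at follow-up. Childhood trauma and personality, taken at baseline, are candidate moderators.

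**The concern.** A moderator that is meant to tell clinicians whom to treat must be known, and untouched by treatment, when the decision is made. A baseline-to-post-treatment change in connectivity is neither. If it is entered as a moderator, its interaction with group mixes three things: the effect of MBSR on the brain, any shared cause of brain change and symptom change, and real differences in benefit. The Conclusion of the article says that clinicians could use the results to target likely responders and tailor treatment. An apparent brain moderator of this kind would not support that use. The MRI analysis section is also the place where the baseline analysis promised in the abstract should be specified, and it does not state one.

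**Working it through.** The plan gives no figure on this point, so the check is mainly a comparison of sections.

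**1. Is the variable measured after randomisation?** The second-level model in MRI analysis has "time (baseline, post-treatment) as fixed factors, as well as a group x time interaction". The Design section says "Participants are randomised into a treatment and a wait-list control group after baseline measurements". A change between those two time points needs the post-treatment scan, so it is a post-randomisation variable.

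**2. Is it expected to respond to treatment?** Yes, by the article's own hypotheses. MBSR is expected to raise SN within-network connectivity during extinction, ECN and SN within-network connectivity during emotional conflict, and both after acute stress. SN and ECN within-network connectivity are the measures given as the example of a moderator.

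**3. Does it precede the outcome?** No. The Post-intervention section places the repeat neurocognitive and clinical assessments at the same pair of visits (3 and 4).

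**4. Do the sections agree?**

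| Section | Baseline measures | Changes |
|---|---|---|
| Abstract, Methods | brain patterns, trauma and personality as moderators | no brain change named |
| Background, aim 4 | predict who benefits | accompany clinical change |
| Clinical symptoms | trauma and personality as moderators | questionnaire changes as mediators |
| MRI analysis | no moderator test stated | given as the example of a moderator |

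MRI analysis is the only section that gives changes the moderator role.

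**5. How far could this mislead?** The article gives no model for the moderator test, so a group x change interaction is assumed here. The following inputs are also assumptions, apart from 54 per group, r = 0.7 and an effect of 0.4 SD, which come from the sample size section.

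- PSS (SD units) = 0.7 x baseline - 0.4 x group - b x engagement x group + error, with error variance 1 - 0.7² = 0.51.
- Connectivity change = 0.5 x group + a x engagement x group + error with SD 1.
- Neither connectivity change nor baseline connectivity enters the PSS equation. Engagement is unmeasured.
- 1,500 simulated trials per row, least squares with robust standard errors, two-sided 5% tests.

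| a / b | group x change significant | group x baseline connectivity significant | mean group coefficient in the change model |
|---|---|---|---|
| 0 / 0 | 3.7% | 5.2% | -0.41 |
| 0.5 / 0.3 | 14.5% | 4.7% | -0.34 |
| 0.7 / 0.5 | 38.2% | 5.3% | -0.28 |

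The largest Monte Carlo standard error of a rejection rate is sqrt(0.382 x 0.618 / 1,500) = 1.3 percentage points.

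The group coefficients can be confirmed by hand. In the MBSR arm the expected slope of PSS on change is -ab/(1 + a²). That is -0.15/1.25 = -0.12 in the second row and -0.35/1.49 = -0.235 in the third. The group coefficient compares the arms at zero change, and the mean change in the MBSR arm is 0.5. It therefore becomes -0.40 + 0.5 x 0.12 = -0.34 and -0.40 + 0.5 x 0.235 = -0.28. It no longer estimates the randomised effect of -0.40.

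**The case against.** The strongest defence is that the wording allows a sound reading. The example is introduced as an example and does not exclude baseline patterns. The word post-treatment qualifies the clinical outcome, not the connectivity. The resting-state section also models connectivity before and after stress induction, and that change is available within the baseline session. This stands as an ambiguity. However, the two-time-point model in the same section makes the longitudinal reading the natural one, and no text states the other.

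Second, the aim-4 sentence does announce a link between change and clinical change: "changes in these measures will be accompanied by changes at the clinical level for aim (4" (the quotation stops at the closing bracket). A reader might infer that MRI analysis contradicts aim 4 altogether. It does not. Only the prediction half, tied to baseline, conflicts. The other half supports relating change to outcome, but as association or mechanism, not as moderation.

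Third, a reader might infer that aim 4 cannot be answered at all. The documents do not support this. Baseline trauma and personality are planned as moderators, and the abstract declares baseline brain patterns.

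Fourth, the reference to patterns that are observed might suggest that candidates will be picked from the trial data at an uncorrected 5% level. The article does not say so. The task sections name SN, ECN and DMN hypotheses in advance, and multiplicity rules for secondary analyses may sit in a document not shown.

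Finally, the moderator work is presented as exploratory in the Discussion summary. That stands, and it lowers the severity.

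**Conclusion.** The concern holds in a limited form. On the natural reading, the only example of a brain moderator in MRI analysis is a post-randomisation variable that MBSR is hypothesised to alter and that is measured at the same visits as the outcome. It cannot show for whom MBSR works. It conflicts with the abstract, with the prediction half of the aim-4 hypothesis, and with the roles set in Clinical symptoms.

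Severity is moderate. The primary ANCOVA, the sample size, the data collection and the trauma and personality moderators are unaffected. The simulated rates of about 14% and 38% depend on assumed loadings and an assumed model. They show direction and possible size only, and with no shared driver the change-score test stayed near its nominal level. The conclusion rests on the comparison of sections, not on those rates.

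**What to change.** Replace the sentence in MRI analysis with two statements.

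1. **Moderation.** Pre-specified baseline within- and between-network connectivity of SN, ECN and DMN is tested through a group x baseline-connectivity term in the PSS ANCOVA, adjusted for baseline PSS. This uses the three tasks scanned at baseline: fear conditioning and extinction, emotional conflict, and resting state. Neurofeedback is added only after the intervention, so it can supply neither a baseline value nor a change. If stress-induced change within the baseline session is intended as a moderator, name it as such.
2. **Change.** Baseline-to-post-treatment change in connectivity is examined as a mediator, or as an exploratory association, with PSS at follow-up as the outcome. This matches the treatment of the questionnaire mediators and gives the right time order.

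The cost is wording only. The baseline scans and follow-up PSS are already part of the schedule, and no sample size or visit changes.

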#### Implicit, exogenous stress-regulation – fear conditioning and extinction task

Based on current fear learning and extinction literature we hypothesise that MBSR will enhance CS differentiation because of clinically promoted awareness to bodily signals and negative affect. We expect this heightened awareness during contextual extinction to lead to better extinction retention at day 2 without affecting fear renewal. Therefore, we expect less spontaneous recovery of the fearful memory when being exposed to the extinguished CS + compared to the CS-. At the physiological level this means that smaller pupil diameter and skin conductance response differences between CS + and CS- are expected in the MBSR group in the early stages of extinction retention compared to the wait-list control group. Similarly, for our self-report measurements, we expect to observe lower perceived fear ratings in the MBSR group in the early stages of extinction retention, differentiating the CS + and CS- compared to the wait-list control group. In our brain imaging measures, we expect that MBSR induces increased connectivity within SN during the extinction phase. We will statistically test differences in outcome physiological measures (skin conductance and pupillometry) between groups with mixed-effect regression analysis on each of the phases of the paradigm (conditioning, extinction, extinction retention, fear renewal). Fixed effects will include stimulus type (CS + , CS-), group (MBSR, wait-list), and time (baseline, post-treatment), as well as a group x stimulus type x time interaction. Additional fixed factors will be added (university, sex, age, and recruitment wave) and a random intercept for participants will be included to account for individual differences. Our main outcome in this task is extinction memory retention a day after extinction learning. Therefore, we will focus on the interaction effect of group x stimulus type x time during the extinction retention phase.

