### Statistical analysis

#### Sample size calculation

The sample size, which is reported on http://trialregister.gov, was calculated on the basis of our planned Analysis of Covariance (ANCOVA) to estimate the difference between groups in perceived stress at post-treatment, while taking into account individual baseline measurements of perceived stress as a covariate. We use the method of Borm, Fransen, & Lemmens (2007), which adjusts the sample size calculated for an independent sample t-test by multiplying with the factor (1-r^2), where r is the correlation coefficient between baseline and post-treatment measurement. We aim to achieve a power of 80% with an *α* = 0.05. The correlation between baseline and end-of-treatment perceived stress is estimated at *r* = 0.7, based on data from Verweij et al. (2018). Assuming a moderate effect size of Cohen's *d* = 0.4, as reported by a large RCT on a general student sample (Galante et al., 2018), we would need 54 participants per group. Taking also into account an average attrition rate (10%) of studies on student populations reported in a meta-analysis by Khoury et al. (2015), we aim to recruit a total of 60 participants per group.

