### Update

We are currently in the process of recruiting and testing participants since April 2021. It is expected that reaching the total sample size which was reported on trialregister.gov will be a challenge. One of the main factors contributing to this is the impact of the COVID-19 pandemic lockdowns, since during the first year of recruitment students were largely studying remotely. In order to address this issue, the study’s recruitment period has been extended by a year, and recruitment efforts have been reassessed. However, there is reason to believe that our sample size estimate is very conservative. The meta-analysis by Khoury et al. (2015) suggests that the combined effect size from studies investigating MBSR on student populations is higher than our original estimate. They report even higher combined effect size on stress measures in studies with various healthy populations, including students. This suggests that our trial is better powered than initially thought. In addition, effect sizes reported in studies investigating the effects of MBSR on stress regulation tasks, similar to the ones we deploy, suggest that the current trial will be well powered to detect these effects [57–60]. This makes us confident that we will be able to detect differences in perceived stress and our stress regulation tasks despite potentially reaching a smaller sample size.

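### The predicted dissociation between extinction retention and fear renewal is not tested by the phase-by-phase models that the article specifies

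*Protocol article*

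**What the plan says.** The analysis section on the fear conditioning and extinction task in the protocol article states the expectation for MBSR: "We expect this heightened awareness during contextual extinction to lead to better extinction retention at day 2 without affecting fear renewal". That is a directional prediction for one phase and a no-effect prediction for another. The design is suited to separating the two: the Methods section on the task places recall in the extinction context and renewal in the original conditioning context.

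The stated method is to compare physiological outcomes "between groups with mixed-effect regression analysis on each of the phases of the paradigm (conditioning, extinction, extinction retention, fear renewal"). The fixed effects are stimulus type, group and time, "as well as a group x stimulus type x time interaction". The section names extinction retention as the task's main outcome: "Therefore, we will focus on the interaction effect of group x stimulus type x time during the extinction retention phase". It gives no term comparing phases, and no interval criterion or margin for renewal.

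The section Sample size calculation bases the numbers on perceived stress alone, says that calculations for the tasks proved very difficult, and cites effects of d = 0.93 to 1.15 for extinction retention. None is cited for renewal. The Update section expects that recruitment may fall short, yet is confident that "we will be able to detect differences in perceived stress and our stress regulation tasks despite potentially reaching a smaller sample size".

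**The concern.** Two separate inferences are missing.

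- A test of a difference cannot support a statement that there is no effect. With no interval criterion, the renewal half of the hypothesis has nothing to stand on except a p-value above 0.05.
- A significant interaction in retention beside a non-significant one in renewal is not evidence that the two interactions differ. That comparison needs its own contrast, and the stated models contain none.

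At stake is a mechanistic conclusion: that MBSR strengthens extinction memory in a context-specific way while leaving the original fear memory as it was. The stated analysis could show that pattern by chance when MBSR shifts both phases equally. A smaller sample makes a true renewal effect easier to miss.

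**Working it through.** **The plan's own figure (perceived stress).** Inputs from Sample size calculation: d = 0.4, r = 0.7, alpha 0.05 (taken as two-sided), power 80%. The t-test size is 2(1.960 + 0.842)² / 0.4² = 98.1, so 99 per group. Multiplying by 1 − 0.7² = 0.51 gives 50.5, so 51; a noncentral-t calculation gives 52. The plan states 54, slightly on the safe side, and 54 / 0.9 = 60. This size is not in dispute. It was not derived for renewal.

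**Inputs for renewal.** n = 54 per arm (from the plan). The baseline to post-treatment correlation r of the CS+ minus CS− score is not given; 0.3, 0.5 and 0.7 are assumed. True effects of 0.4 SD (borrowed from perceived stress), 0.5 SD (assumed) and 0.93 SD (the lower value cited for retention) are tried. A shortfall to 45 per arm is assumed, because the Update section gives no number.

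**Standard error.** I treat the three-way interaction as a two-sample comparison of change in the CS+ minus CS− score. In SD units the SD of change is √(2(1 − r)), so SE = √(2(1 − r)) × √(2/54).

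| | r = 0.3 | r = 0.5 | r = 0.7 |
|---|---|---|---|
| SE | 0.228 | 0.192 | 0.149 |
| 95% CI half-width (1.96 × SE) | 0.45 | 0.38 | 0.29 |
| Missed, 0.4 SD, 54 per arm | 59% | 46% | 24% |
| Missed, 0.5 SD, 54 per arm | 41% | 27% | 9% |
| Missed, 0.4 SD, 45 per arm | 65% | 53% | 32% |
| Missed, 0.5 SD, 45 per arm | 49% | 35% | 14% |
| Missed, 0.93 SD, 54 per arm | 2% | under 1% | under 1% |

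Example: 0.4 SD with r = 0.5 gives an expected test statistic of 0.4 / 0.192 = 2.08, barely above 1.96, so the test misses in 46% of trials.

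**False dissociation.** Let both phases have the same true effect, and let the two test statistics be bivariate normal with correlation 0.3 to 0.7 (assumed). The probability that retention is significant and renewal is not, at 54 per arm, is:

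| True effect in both phases | r = 0.3 | r = 0.5 | r = 0.7 |
|---|---|---|---|
| 0.4 SD | 12–20% | 13–20% | 10–15% |
| 0.5 SD | 12–20% | 10–16% | 5–7% |
| 0.93 SD | 1–2% | under 1% | under 1% |

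Ranges within a cell reflect the correlation between the statistics; the largest value in the 0.93 SD row is below 2%. Among trials with significant retention only, the overall ranges are 13–47% (0.4 SD) and 5–33% (0.5 SD).

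**A direct phase contrast.** If the true effects are equal, a two-sided test of the phase difference at the 5% level errs in 5% of trials. Its standard error is the single-phase SE times √(2(1 − k)), where k is the correlation between the two phase estimates: factors of 1.18, 1.00 and 0.77 for k = 0.3, 0.5 and 0.7. So it need not be much less precise than the tests already planned.

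**Can the no-effect half be shown at all?** Take 0.5 SD as an illustrative limit; the documents give none. With a true effect of zero, the chance that the 95% interval lies inside ±0.5 SD is 2Φ(0.5/SE − 1.96) − 1: about 19%, 48% and 84% for r = 0.3, 0.5 and 0.7.

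**The case against.** A reader might infer that the investigators will treat a non-significant renewal result as proof of no effect. The document does not say so. The clause is an expectation, no decision rule is attached to it, and the stated focus is the retention phase. The point is therefore about what the stated models can support, not about a conclusion already announced.

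The other objections carry weight too. Renewal is a non-primary phase of one of four mechanistic tasks, and the operational predictions for pupil size, skin conductance and fear ratings all concern retention. The 0.4 SD benchmark belongs to perceived stress. At effects as large as those cited for retention, the renewal test would seldom miss. The figures come from a difference-score approximation; the planned random-intercept model may give other standard errors. All of this stands and limits the size of the point.

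It can also be said that margins and follow-up contrasts belong in an analysis plan that is not shown. For a margin, that is fair. For the model structure it is less so: the article fixes the models phase by phase down to the interaction term, and an analysis plan that followed this text would carry the mismatch forward. Finally, an equivalence test is not an easy cure, since at 54 per arm it would often be inconclusive even if renewal were truly unaffected.

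**Conclusion.** The concern holds in a limited form. The hypothesis is a dissociation, and the stated models test neither its no-effect half nor the difference between phases. At 54 per arm, the renewal test misses 24–59% of true effects of 0.4 SD and 9–41% of those of 0.5 SD. Equal true effects would look like a dissociation in about 10–20% and 5–20% of trials respectively. These figures rest on assumed correlations, assumed effect sizes and a difference-score approximation; at 0.93 SD in both phases the false dissociation falls below 2%. The claim that the renewal test would usually miss a relevant effect is not supported in general, because it depends on inputs that the documents do not give. The perceived-stress analysis, its sample size and the retention-phase test are untouched.

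**What to change.** Keep the retention-phase interaction as the task's main test. Then:

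1. Add one joint model of the retention and renewal phases with a group by stimulus type by time by phase term, and name it as the test of the dissociation. Its random effects should allow for both phases coming from the same participant; a participant-level contrast does this simply.
2. Report the renewal effect with its 95% confidence interval. Word a non-significant result as no evidence of a difference, unless the interval excludes effects that the investigators declared relevant beforehand. The choice of that limit is theirs.
3. If no such limit can be justified, label the renewal expectation exploratory.

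The cost is one extra secondary model on data already collected, and some wording. The real downside is that, at this sample size or a smaller one, the data may well be unable to establish that renewal is unaffected. It is better to say so before the results are known.

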#### Explicit, exogenous stress-regulation – emotional conflict resolution task

We will explore explicit, exogenous regulation by assessing behavioural responses and brain activity during a Stroop-like emotional conflict resolution task as described by Etkin et al. (2006). This task requires explicit attentional control and response inhibition over emotional processing that arises from conflicting external emotional information. The task consists of 148 presentations of happy or fearful facial expression photographs chosen from the set of Ekman and Friesen (1976). Faces are cropped and the words ‘‘FEARFUL’’ or ‘‘HAPPY’’ are written across the face in Dutch (i.e. “BANG”, “BLIJ”), such that word and expression are either congruent or incongruent. Stimuli are presented for 1 s, with a varying interstimulus interval of 3–5 s, during which a central fixation cross is shown. Participants are instructed to respond as fast and accurately as possible, by selecting the response buttons corresponding to ‘‘fearful’’ or ‘‘happy’’ for the expression on the face. This task is designed to probe emotional conflicts by manipulating the congruency of the stimuli. Congruency refers to whether the two types of stimuli shown simultaneously in this experiment (i.e., facial expression and written word) match or not. For example, when a facial expression matches the word superimposed on it is considered a congruent trial, and when the facial expression does not match the word superimposed on it is considered an incongruent trial.

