#### Explicit, exogenous stress-regulation – emotional stroop task

We expect that MBSR will affect participants’ responses when they are asked to identify and respond to emotionally conflicting information. In terms of behaviour, we expect to observe this as a reduction in response time in incongruent emotional situations. On our brain imaging measurements, we expect that MBSR will enhance ECN and SN within-network connectivity during emotional conflict processing. We will statistically test differences in behavioural outcome measures (reaction time and accuracy) between groups with linear mixed-effect regression analysis. Fixed factors will include group (MBSR, wait-list), time (baseline, post-treatment), congruency (congruent, incongruent), as well as a group x congruency x time interaction. Additional fixed factors will be added (university, sex, age, and recruitment wave) and a random intercept for participants will be included to account for individual differences.

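### The fear-task and Stroop models state only a participant random intercept, so person-specific change in the condition effect between sessions has no term and the three-way tests are not reliably at 5%

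*Protocol article*

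**What the plan says.** In the Protocol article's analysis section for the fear conditioning and extinction task, skin conductance and pupil size are analysed by "mixed-effect regression analysis on each of the phases of the paradigm". The fixed effects are stimulus type, group and time, "as well as a group x stimulus type x time interaction", plus demographic and wave covariates. For the random part, the text says that "a random intercept for participants will be included to account for individual differences". The main result is named: "we will focus on the interaction effect of group x stimulus type x time during the extinction retention phase". The hypothesis in that section concerns the early part of retention.

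The emotional Stroop section uses the same structure for reaction time and accuracy: group, time and congruency, "as well as a group x congruency x time interaction", again with a participant random intercept as the one random term named. The task description says: "The task consists of 148 presentations of happy or fearful facial expression photographs". The number of CS presentations per phase is not given. Neither section says whether single trials or one mean per participant, condition and session enter the model.

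**The concern.** Each participant contributes to four cells: two conditions at two sessions. The tested effect is a difference of differences within the person, compared between groups. Its correct error has two parts: trial noise, and the spread between people in how far their condition effect changes from baseline to post-treatment. A random intercept captures neither that spread nor a person's shift in overall level between sessions. Both fall into one pooled residual.

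At stake is the calibration of the main fear-task result and of the Stroop behavioural result, which serve the stress-regulation aims. With many trials per cell, the standard error can follow the number of trials rather than the number of people.

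**Working it through.** The article gives no error rate or variance for these models, so there is no stated figure to reproduce.

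**Inputs from the document.** 54 per group after attrition ("we would need 54 participants per group") and alpha 0.05, both from the PSS sample size calculation and taken here as two-sided; 148 Stroop presentations per session.

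**Assumptions.** Balanced congruency, so 148/2 = 74 trials per cell. Stroop trial SD σ = 150 ms. Session-specific congruency effect with between-person SD s = 10, 20 or 30 ms. For the fear task, n = 4 or 10 trials per CS and s = 0.25σ or 0.5σ. The effects are independent between sessions unless a correlation ρ is stated.

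**Single trials.** A person's three-way contrast has true variance 4σ²/n + 2s²(1 − ρ). The random-intercept model credits it with about 4σ²/n. So

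ratio = 1 + n·s²·(1 − ρ)/(2σ²), and type I error = 2[1 − Φ(1.96/√ratio)].

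The number of participants cancels from the ratio.

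| Task | n | s | Ratio at ρ = 0 | Type I, ρ = 0 | ρ = 0.5 | ρ = 0.8 |
|---|---|---|---|---|---|---|
| Stroop | 74 | 10 ms | 1.164 | 6.9% | 6.0% | 5.4% |
| Stroop | 74 | 20 ms | 1.658 | 12.8% | 8.9% | 6.5% |
| Stroop | 74 | 30 ms | 2.480 | 21.3% | 13.7% | 8.5% |
| Fear | 4 | 0.25σ | 1.125 | 6.5% | 5.7% | 5.3% |
| Fear | 4 | 0.5σ | 1.500 | 11.0% | 8.0% | 6.2% |
| Fear | 10 | 0.25σ | 1.313 | 8.7% | 6.8% | 5.7% |
| Fear | 10 | 0.5σ | 2.250 | 19.1% | 12.4% | 8.0% |

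Example, Stroop at 20 ms: 1 + 74 × 400/(2 × 22,500) = 1.658; 1.96/√1.658 = 1.522; two-sided tail 12.8%. Simulation with 54 per group gave 6.9%, 12.1% and 20.7% for 10, 20 and 30 ms.

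**Stable differences.** At ρ = 1 the extra term is zero. Simulation with a stable slope of 0.3-0.6 trial SD gave 4.4-4.8% (Stroop) and 4.2-4.4% (fear, 12 trials), so there was no inflation.

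**Cell means.** Here the error variance per cell mean is e = 150²/74 = 304 ms². Suppose each person's overall level also shifts with SD τ = 30 ms at each session. On a common scale, the condition and the condition-by-time contrasts each have variance e + s²/2, and the time contrast has e + 2τ² = 304 + 1,800 = 2,104. The model uses their average for all three.

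| s | Condition-by-time variance | Pooled residual | Three-way ratio, type I | Group by time ratio, type I |
|---|---|---|---|---|
| 10 ms | 354 | (2 × 354 + 2,104)/3 = 937 | 0.378, 0.1% | 2.245, 19.1% |
| 20 ms | 504 | (2 × 504 + 2,104)/3 = 1,037 | 0.486, 0.5% | 2.028, 16.9% |
| 30 ms | 754 | (2 × 754 + 2,104)/3 = 1,204 | 0.626, 1.3% | 1.747, 13.8% |

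Simulation agreed: 0.2-1.6% for the three-way test and 14-19% for group by time.

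**Comparator.** Testing each person's own condition-by-time contrast between groups gave 4.2-5.9% in every setting of the simulation grid.

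**The case against.** The strongest reply is that the unit of analysis is not stated. Accuracy is placed in a linear model, which suits aggregated proportions at least as well as binary trials. In a grid with one mean per cell, the three-way test ran at 3.8-5.8%. This stands as a limit on any one-directional claim, but it does not rescue the model. That grid had at most a small session shift in overall level, and its change in condition effect was at most 0.6 of the cell-mean error SD. With a larger level shift, the pooled residual is wrong for both tests, as shown above. Group by time is not the interaction that the two sections name. It still matters for Stroop, because the behavioural hypothesis there is faster responding in incongruent trials.

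A reader might infer that any difference between people in the condition effect inflates the test, and cite the aim of finding who benefits most. The documents do not support that: stable differences cancel, and no variance is given for the change between sessions.

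A reader might also infer that the plan pools the whole retention phase against its own early-phase hypothesis. The text names the phase for the test but does not say that all its trials enter.

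A condensed article may leave random slopes to a fuller document. That is fair for omitted detail, but here a random structure is stated, twice, and it does not match the tested effect.

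**Conclusion.** The point holds in a conditional form. As stated, the models have no term for person-specific change in the condition effect between sessions. With single trials and the assumed variances, type I error is about 7-21% for Stroop and about 6-19% for the fear task. At the lower end, or with a high correlation between sessions, the excess is slight. With cell means and a shift in overall level, the three-way test is conservative and group by time anticonservative.

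A flat statement that the intervals will be too narrow would go too far, because the direction depends on a unit of analysis that the article does not give. What can be said is that neither unit makes this model a dependable 5% test. All variances, the fear trial counts and the balanced Stroop cells are assumptions. These are mechanistic outcomes, so the primary PSS ANCOVA is untouched. The change should still be made before analysis.

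**What to change.** Compute one condition contrast per participant per session. For the fear task this is CS+ minus CS- in extinction retention, using a pre-defined window of the early trials that the hypothesis names. For Stroop it is incongruent minus congruent reaction time. Compare groups on the post-treatment contrast by ANCOVA with the baseline contrast as covariate, keeping the covariates already listed. This is the form already planned for PSS, and with one outcome value per person there is no within-person residual to misspecify.

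Alternatively, keep trial-level models, say so, and add by-participant random slopes for condition, time and condition by time, with all lower-order fixed interactions. A random slope for condition alone would not be enough.

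The cost is wording and script changes; no new data are needed. Intervals may be wider than from a trial-level random-intercept model, and the random slopes may need simplifying if the model does not converge.
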